### Objectives

Our primary objective is to demonstrate the superiority of the intensified short course (6 months) ATT regimen containing high-dose rifampicin and moxifloxacin and standard ATT regimen (12 months) in reducing composite outcome of mortality or disability among adults with TBM. Secondary objectives are to assess the safety and tolerability of high-dose rifampicin and moxifloxacin when given daily for 8 weeks and pyrazinamide administration for 6 months. We also aim to compare the pharmacokinetic (PK) parameters of ATT in the serum and cerebrospinal fluid (CSF) between the three arms, and to compare the health-related quality of life between the intervention and control arms.

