### Treatment allocation

#### Arm 1 (intensified ATT with aspirin)

Participants in this arm will receive a high dose of rifampicin 25 mg/kg once daily and moxifloxacin (400 mg once daily) along with isoniazid and pyrazinamide for 2 months. Steroids will be administered to participants with MRC grades 1 and 2 for a duration of 6 weeks, while participants in grade 3 will be treated for 8 weeks. This regimen will also be intensified with 150 mg of aspirin once daily. Intensive phase will be followed by standard doses of rifampicin, isoniazid, and pyrazinamide for the next 4 months in the continuation phase (Fig. 1).

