#### Arm 3 (control arm)

The control arm will receive treatment according to the standard national guidelines for TBM. They will receive a first-line regimen consisting of 2 months of isoniazid, rifampicin, ethambutol, and pyrazinamide followed by 10 months of isoniazid, rifampicin, and ethambutol daily in a fixed-dose combination (FDC) as per the various weight bands in National TB Elimination Programme of India. Participants will also receive steroids as in the other two arms.

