### Participant timelines and follow-up

In this assessment, demographic details, medical history, clinical examination, neurological assessment including Modified Rankin Score (MRS) and Glasgow Coma Scale (GCS), sociological assessment for compliance to trial procedures, and all other study procedures will be done. Blood will be collected for hematological (complete blood count—CBC) and biochemical tests (sugar, HbA1C, liver, and renal function tests), HBsAg, and HIV. Patients will also undergo CT or MRI imaging of the brain. We will also collect sputum for CBNAAT and AFB culture and do chest X-ray to rule out pulmonary TB. All eligible patients will be enrolled into the trial. At the time of enrolment, blood will be collected for immunological biomarkers (CRP, TNF-α, monocyte and dendritic cell functions, and other cytokines).

During the study period, patients will be followed as per the study schedule attached (Table 1). After admission to the study and treatment allocation, participants will be followed up every week for the first 2 months and monthly till the completion of the treatment. They will undergo clinical examination including detailed neurological examination and adverse event (AE) monitoring. After treatment completion, all participants will be followed up once in 3 months for a period of 12 months. Participants in the study arms I and II will complete 12 months of post-treatment follow-up at the 18th month study visit and participants in the control arm will complete their post-treatment follow-up at the 24th month study visit.

**Table 1 Tab1:** Study schedule

S No	Investigations	Pre-screening	Screening	Enrolment	W1	W2	W3	W4	W5	W6	W7	W8	M3	M4	M5	M6	M7	M8	M9	M10	M11	M12	M15	M^a^18	M21	M24
1	Screening consent		✓																							
2	Assess eligibility		✓	✓																						
3	Informed consent			✓																						
4	History and clinical examination		✓	✓	✓	✓	✓	✓	✓	✓	✓	✓	✓	✓	✓	✓	✓	✓	✓	✓	✓	✓	✓	✓	✓	✓
5	GCS		✓	✓	✓	✓	✓	✓	✓	✓	✓	✓	✓	✓	✓	✓			✓			✓	✓	✓	✓	✓
6	Modified Rankin’s score		✓	✓	✓			✓				✓		✓		✓			✓			✓	✓	✓	✓	✓
7	Sputum smear and MGIT^b^		✓																			✓		✓		
8	CSF analysis for AFB smear, MGIT, Xpert, and to rule out other etiology as appropriate	✓																								
19	CSF cytology, biochemistry,	✓																								
10	HIV		✓																							
11	Urine pregnancy test^c^		✓					✓				✓	✓	✓	✓	✓	✓	✓	✓	✓	✓	✓				
12	Hepatitis B and C		✓																							
13	LFT		✓			✓		✓		✓		✓		✓		✓			✓			✓				

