14	RFT		✓			✓		✓		✓		✓		✓		✓			✓			✓				
15	Uric acid					✓		✓		✓		✓		✓		✓										
16	HbA1C (only for diabetics)		✓										✓			✓			✓			✓				
17	Hematology		✓					✓				✓				✓			✓			✓				
18	CD4 count if HIV positive		✓					✓				✓				✓			✓			✓				
19	Imaging (CT/MRI)		✓													✓										
20	CXR^b^		✓																							
21	ECG in 12 leads		✓					✓				✓				✓										
22	Intensive PK Serum^d^					✓																				
23	Sparse PK Serum					✓		✓				✓														
24	CSF PK (single time point)^d^																									
25	Adverse event assessment			✓		✓	✓	✓	✓	✓	✓	✓	✓	✓	✓	✓	✓	✓	✓	✓	✓	✓				
26	Storage of plasma and serum sample		✓					✓				✓				✓			✓			✓				
27	Neurological assessment			✓	✓	✓	✓	✓	✓	✓	✓	✓				✓			✓			✓		✓		✓
28	Quality of life assessment			✓												✓						✓		✓		✓

^a^Participants in the intervention arm will complete 12 months of post-treatment follow-up at 18th month study visit and participants in the control arm will complete their post-treatment follow up at 24th month study visit

^b^At baseline and when symptomatic

^c^Urine pregnancy test in women with reproductive potential

^d^Intensive PK serum and CSF to be planned between weeks 1 and 2

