### Adverse event (AE) management

The participants will be closely monitored during the scheduled study visits. AEs will be collected from the initiation of treatment regimen onwards. All serious adverse events (SAEs) occurring during the trial period must be reported to the Institutional Ethics Committee (IEC) i.e., within 24 h of the investigator becoming aware of the event. They will also be reported to the sponsor and the competent authorities within the specified period of time as defined in New Drugs and Clinical trials Act 2019. The AEs will be graded as per DAIDS grading Table 2017 and managed as per protocol especially for grade III and grade IV events, hepatotoxicity, and cardiovascular system events [19].

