The analysis for the primary outcome will be stratified based on HIV status and baseline severity of the disease measured by MRC. Sensitivity analysis will also be done including only definite and probable cases of TBM. The Cox proportional regression will be summarized using hazard ratio and 95% confidence interval. Extended Cox regression will be used in lieu of proportion Cox regression if the proportional hazard assumption is violated. The AE data will be summarized using frequency and percentage and compared between the regimens using Chi-square test. In addition, count regression models will be used to compare the number of AEs between the regimens after adjusting for other variables. Maximum plasma concentration (*C*max), time for maximal concentration (*T*max), and area under the curve (AUC) will be measured and correlated with treatment outcomes and occurrence of adverse events using log binomial regression model. Influence of PK parameters on treatment outcome will be identified using multivariable regression analysis. The quality of life will be summarized using mean and standard deviation. The variable will be compared between the regimens using ANOVA or the non-parametric alternative, Kruskal–Wallis test.

We will deal the missing data using multiple imputation technique depending on the missing data mechanism.

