### Outcome measures

Our primary outcome is mortality or disability which will be measured between inclusion and month 12 and month 24, i.e., time from randomization to death or disability during the follow-up period. All-cause mortality also will be considered as an outcome in the study. Survivors will be censored at the date they were last known to be alive (i.e., date of last follow-up visit, loss to follow-up or withdrawal). All-cause mortality rate will be measured in proportion and disability will be measured by modified Rankin scale. We will classify the score as “no disability” (a score of 0), “mild to moderate disability” (score of 1–2), and “severe disability” (3–5).

Grade 3 or 4 AEs will be measured in proportion according to Division of AIDS (DAIDS) criteria at the end of 12 months [18]. The DAIDS criterion categorizes adverse events as “mild events” (grade 1), “moderate events” (grade 2), “severe events” (grade 3), and “potentially life threatening events” (grade 4). Pharmacokinetic outcome measures will be plasma concentration time-curve during the dosing interval (AUC), peak plasma concentration (*C*_max_), and CSF concentration. Time to reach maximum plasma concentration (*T*_max_) of the study drugs will be measured up to week 8. Quality of life at baseline and 6 months, 12 months, and 24 months will be assessed in mean and standard deviation using a WHO Short form-36 (SF-36) questionnaire. It is a commonly used generic health-related quality of life (QoL) instrument which consists of 36 questions measuring health in different dimensions covering physical, mental, and social well-being of the patients. SF-36 was adapted and translated into several language and its validity and reliability were already established in India in TB context [22, 23].

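### The single 12-month grade 3–4 adverse event proportion does not match the 8-week and 6-month safety objective and can dilute an excess in the intensified arms

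*Protocol article*

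**What the plan says.** The Objectives section sets out to "assess the safety and tolerability of high-dose rifampicin and moxifloxacin when given daily for 8 weeks and pyrazinamide administration for 6 months". Under Outcome measures, the severe-event outcome is: "Grade 3 or 4 AEs will be measured in proportion according to Division of AIDS (DAIDS) criteria at the end of 12 months". Under Data analysis, adverse event percentages are compared by chi-square test and, in addition, "count regression models will be used to compare the number of AEs between the regimens". Under Adverse event (AE) management, "AEs will be collected from the initiation of treatment regimen onwards".

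Treatment lengths differ. After the 2-month intensive phase, arm 1 receives "standard doses of rifampicin, isoniazid, and pyrazinamide for the next 4 months in the continuation phase", and arm 2 does the same. The control arm's 2-month intensive phase is "followed by 10 months of isoniazid, rifampicin, and ethambutol daily".

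Under Participant timelines and follow-up, "participants will be followed up every week for the first 2 months and monthly till the completion of the treatment", with adverse event monitoring, and then once every 3 months. In Table 1, the row "Adverse event assessment" is ticked at enrolment, W2–W8 and every month from M3 to M12. W1 is blank, nothing is ticked after M12, and no footnote separates the arms.

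**The concern.** The objective asks about the toxicity of drugs given for 8 weeks and 6 months. The only grade 3–4 comparison stated runs to 12 months. The added half-year contains study drugs in control only and, by the text, closer observation of control. Both features tend to add recorded control events and add little in arms 1 and 2. If the intensified regimen causes more severe events early on, the one proportion that reports on it can understate the difference, and a reader could take a diluted result as reassurance.

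Table 1 raises two smaller questions. It shows no adverse event assessment at W1, although the text has weekly visits with monitoring. It also shows monthly assessment in months 7–12 for arms that the text has moved to 3-monthly visits.

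**Working it through.** The document gives no adverse event rate, so there is no planned figure to reproduce. The check compares exposure and visits, then illustrates the size on assumed rates.

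**1. Months on study drugs within the 12-month window** (treatment allocation sections)
- Control: 2 + 10 = 12.
- Arms 1 and 2: 2 + 4 = 6.

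**2. Scheduled visits by the text** (Participant timelines and follow-up)
- To month 6, all arms: 8 weekly + 4 monthly (M3–M6) = 12. The schedule is identical.
- Months 7–12, control: M7–M12 = 6. Total 18.
- Months 7–12, arms 1 and 2: M9 and M12 = 2. Total 14.

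**3. Assessments by the adverse event row of Table 1**
- After enrolment, every arm: W2–W8 (7) + M3–M12 (10) = 17.
- The row conflicts with the text at W1 (blank, though other rows show a W1 visit) and, for arms 1 and 2, at M7, M8, M10 and M11 (ticked, though the text gives those arms no visit).
- Liver and renal function tests are ticked at M9 and M12 for all arms, so by the table the laboratory schedule in months 7–12 does not differ.

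**4. Illustration on assumed rates**

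Let p be the risk of a grade 3–4 event by month 6, and q the probability that an event-free patient has a first recorded event in months 7–12. The cumulative 12-month risk is p + (1 − p)q. Deaths and losses are ignored. Power is for one intensified arm against control, two-sided 5%, n = 124 per arm (Sample size section):

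power = Φ{[|p1 − p2| − 1.96√(2p̄(1 − p̄)/n)] / √([p1(1 − p1) + p2(1 − p2)]/n)}

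Assume p = 25% intensified and 10% control, a difference of 15 points with power 0.88.

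| q control | q intensified | 12-month control | 12-month intensified | Difference (points) | Power |
|---|---|---|---|---|---|
| 0 | 0 | 10.0% | 25.0% | 15.0 | 0.88 |
| 2% | 1% | 11.8% | 25.75% | 13.95 | 0.81 |
| 5% | 1% | 14.5% | 25.75% | 11.25 | 0.60 |
| 10% | 2% | 19.0% | 26.5% | 7.5 | 0.29 |
| 15% | 2% | 23.5% | 26.5% | 3.0 | 0.08 |

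For example, in the fourth row control is 0.10 + 0.90 × 0.10 = 0.190 and intensified is 0.25 + 0.75 × 0.02 = 0.265.

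Other assumed starting points:
- 20% v 10% at month 6 (10 points): the same four non-zero pairs of q give 9.0, 6.3, 2.6 and −1.9 points.
- 30% v 20% at month 6 (10 points), with q = 2% intensified: q = 5% in control gives 0.314 − 0.240 = 7.4 points, and q = 10% gives 0.314 − 0.280 = 3.4 points.

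**The case against.** The strongest reply is that the 12-month window is a legitimate choice. The trial compares a 6-month regimen with a 12-month one, and toxicity in the control arm's extra six months is a real consequence of that regimen. Counting it over equal calendar time is not a bias in itself. This stands, and it is why the 12-month proportion should be kept. It answers a whole-regimen question, however, and the stated objective is about 8 weeks and 6 months.

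Several stronger readings are tempting, and the document does not support them.

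- A reader might infer a snapshot at month 12, with intensive-phase toxicity hidden. Events are collected from the start of treatment, so the proportion is most naturally cumulative and early events count. An excess is diluted, not erased.
- A reader might take six against two adverse event assessments as settled. It follows from the text, but Table 1 ticks the assessment monthly for all arms. If the table governs, the visit imbalance disappears; the 12 against 6 months of drug exposure remains.
- A reader might infer that the adverse event counts have no common window. The Table 1 row ends at M12 for every arm.
- A reader might infer from the blank W1 cell that first-week events are lost. Weekly monitoring is in the text, the W1 visit has clinical and neurological examination, and doses are supervised except on Sundays. The blank is an inconsistency to correct.

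The data and safety monitoring board also receives reports after 33% and 66% of enrolled patients have completed 8 weeks of treatment. This protects participants during the trial but does not change the comparison finally reported. An exposure offset in the count models is analysis-plan detail, and its absence from an article is no fault.

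**Conclusion.** The point holds as a mismatch between objective and outcome window that can dilute an excess of severe toxicity in arms 1 and 2. That the window contains 12 months of drug in control and 6 in arms 1 and 2 is certain from the document. The visit imbalance in months 7–12 holds by the text only. The size cannot be fixed from the document: under the assumed rates it runs from negligible to near-complete loss of the excess, and in one extreme case to a small reversal. It would be wrong to say that toxicity is masked; that depends on late event rates which are not given. The conflicts between Table 1 and the text, at W1 and in months 7–12, are real but minor.

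**What to change.** - Add comparisons of the proportion with a grade 3 or 4 event by week 8 and by month 6, and name them as the analyses that answer the safety objective. The visit schedule to month 6 is the same in all arms.
- Keep the 0–12 month proportion as the whole-regimen comparison.
- In Table 1, schedule adverse event assessment at W1, in line with the text.
- State whether the adverse event ticks at M7, M8, M10 and M11 apply to arms 1 and 2, and make text and table agree.

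The cost is small: two more safety comparisons from data already to be collected, at a visit schedule that already exists, and a table correction. The article reports that recruitment had not begun.

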### Ethical considerations

This study will be conducted in accordance and compliance with Indian standards of Good Clinical Practice (Indian GCP), ICH-GCP, Declaration of Helsinki (WMA, 2013), CDSCO guidelines, Ethical Guidelines for Biomedical Research on Human Participants 2017 (Indian Council of Medical Research, New Delhi), applicable Government of India Regulations, and research policies and procedures of the institute. This trial has been registered prospectively with Clinical Trial Registry of India and ClinicalTrials.gov with the registration numbers CTRI/2023/05/053314 and NCT05917340, respectively. All participants during pre-screening and screening will be given participant’s information sheet and obtained written informed consent. Participants will be informed that their participation is voluntary and that they may withdraw from the trial at any time. If a participant is unable to give the consent participant due to altered sensorium or severely illness, the consent will be taken by the legally acceptable/authorized representative (LAR) and a re-consent will be taken once the participant has ability to understand the study procedure and in a position to give consent. The confidentiality of the participant’s details will be ensured. Consent will also be obtained for use of biological samples in the future. The results of trial will be published in peer-reviewed medical journals and disseminated at national and international conferences. ICJME criteria will be adhered while defining the authorship. Any modifications, deviation, and amendments to the protocol will be intimated to the ethics committees of ICMR-NIRT and respective sites time-to-time. The informed consent form will be revised as per protocol amendments and re-consent will be obtained will be obtained from the participants after sharing the relevant information.

### Confidentiality

The processing of personal data in this trial will be limited to those data that are reasonably necessary to investigate the anti-bacterial activity, safety, and tolerability of the investigational product used in this trial. These data will be processed with adequate precautions to ensure confidentiality.

The study participant will be informed during the informed consent process that—the investigators, monitors, the auditors, the IEC, and the regulatory authorities will be granted direct access to the participant’s original medical records for verification of clinical trial procedures and/or data, without violating the confidentiality of the participant, to the extent permitted by the applicable laws and regulations and that, by signing a written informed consent form, the participant or the participant’s legally acceptable representative is authorizing such access. The participants will not be identified in any presentations or publications based on the results of this research. The sponsor or its representatives whose responsibilities require access to personal data are obliged to keep the identity of trial participants confidential. This confidentiality will be maintained throughout the complete data processing. We do not have plans of granting access to full protocol, participant level data set, or statistical code at the moment. However, we may do so once the findings of the trial are disseminated.

### Ancillary and post-trial care

Participants enrolled into the trial will be covered by insurance for non-negligent harm associated with the protocol. This will include cover for additional health care, compensation for trial-related injury, and death. ICMR-NIRT will facilitate this compensation through insurance based on the recommendation of the ethics committee.

## Discussion

Our trial is one of the attempts to reduce the high morbidity and mortality associated with TBM. High-dose rifampicin has been proved to be efficacious in patients with pulmonary TB. A meta-analysis of eight studies reporting on higher doses of R (13 to 35 mg/kg) in patients with pulmonary TB demonstrated accentuated sputum culture conversion as compared to the standard-dose group. The authors also reported no increased adverse events in the high dose rifampicin group [24]. Rifampicin in the current dosages and ethambutol used in the current regimen for the management of TBM have limited CNS penetration. In patients with TBM, high doses of rifampicin are associated with increased CSF exposure, improved clinical outcomes without increased grade III or IV adverse events [25–27].

Ruslami et al. showed a 50% reduction in mortality compared to the standard oral dose (10 mg/kg) when participants were given a higher dose of intravenous rifampicin (13 mg/kg/day) in adults with TBM in Indonesia. The trial also compared ethambutol (750 mg) with moxifloxacin (400 mg vs 800 mg). Hepatotoxicity of all grades was equally distributed across the groups [25]. Higher dose of rifampicin did not increase drug-related AEs and improved the survival of patients [25]. Dian and colleagues administered three different oral doses of rifampicin (10 mg/kg vs 20 mg/kg vs 30 mg/kg) along with isoniazid, pyrazinamide, and ethambutol and compared with standard TB regimen in adults with TBM. They also demonstrated lower incidence of 6-month mortality without increase in the incidence of grade 3 and 4 AEs [27]. High-dose intravenous and oral rifampicin were found to be safe in the trial. Adults from Uganda who were suspected of having TBM were randomized to receive high-dose oral rifampicin (PO-35, 35 mg/kg/day), intravenous rifampicin (IV-20, 20 mg/kg/day), or standard-of-care control (PO-10, rifampicin 10 mg/kg/day) along with isoniazid, pyrazinamide, and ethambutol. The composite safety endpoint did not differ between the three arms (*P* = 0.342). Rifampicin exposure in the CSF was approximately eightfold higher in the oral high dose arm (35 mg/kg) than the standard of care with no additional toxicity [28].

Charlie et al. conducted a meta-analysis of five trials that included 1028 participants with TBM. They reported that though high-dose of rifampicin did not reduce mortality, there was no significant increase in the risk of grade 3–5 adverse events. The authors recommended that future trials are required to conclude on the optimal dose of rifampicin and the efficacy of such a high dose in reducing mortality among patients with TBM [29]. In summary, doses up to 25 mg/kg to 35 mg/kg appear safe in studies from Africa and Asia, but large-scale studies evaluating clinical efficacy are needed.

Thwaites et al. demonstrated better CSF penetration among TBM patients when given ciprofloxacin (750 mg every 12 h) or levofloxacin (500 mg every 12 h) or gatifloxacin (400 mg every 12 h) in addition to conventional four-drug regimen. Among the agents, CSF penetration was greatest with levofloxacin [30]. Allfennar and colleagues concluded that though moxifloxacin enters the CSF at the same rate as levofloxacin, it accumulates well in the CSF and thus has the theoretical advantage of greater in vitro activity against M. tb than levofloxacin [31].

Current WHO guidelines 2022 recommend 4-month moxifloxacin-containing regimen with rifapentine and INH for 4 months along with pyrazinamide in the initial 2 months for pulmonary TB. However, this regimen is not recommended for TBM at this juncture due to a lack of evidence [32]. Pyrazinamide is unique as it works against the non-replicating persisters and has a sterilizing activity and good CNS penetration. One of the earlier clinical observations from India using 1500 mg of pyrazinamide along with isoniazid 300 mg and rifampicin 450 mg. Pyrazinamide was continued after the intensive phase, and it was observed that no patients presented with new symptoms suggesting focal deficit and/or increased intracranial pressure during follow-up [33]. Another prospective cohort study from South Africa also confirmed similar findings. However, this has not been studied in a RCT yet [34].

While the mortality due to TBM among hospitalized patients was 42%, disability among them has been reported as 32% leading to poor quality of life among survivors [7, 35]. This highlights the importance of measuring disability as a primary outcome in addition to mortality. Evidence suggests that aspirin reduces the new-onset stroke, a major cause of disability in patients with TBM by significantly reducing perivascular inflammation. According to a meta-analysis with 365 participants from three randomized trials, aspirin effectively decreased the incidence of new-onset stroke with a number needed to treat of 10 [36]. The doses of aspirin used in these trials also varied widely. A trial from India showed lower dose aspirin (150 mg/day) when used along with steroids prevented new infarcts and reduced strokes and mortality [37]. In contrast, Schoeman et al. demonstrated in an open-label trial that aspirin use, regardless of dosage, did not significantly reduce mortality and morbidity (hemiparesis) [38]. Hence, it is vital to prove the efficacy of aspirin in reducing the stroke with an adequate dose for an appropriate period. Thus, we propose 150 mg of aspirin to all TBM patients in one of the intervention arms for 2 months. Thwaites et al. showed in a large RCT, that while there is a significant reduction in mortality in the steroid group, the proportion of patients with severe disability was higher (18.2 vs 13.2%) [39]. An almost-quarter reduction in mortality was observed with the use of steroids, according to a systematic review and meta-analysis comprising 9 trials involving 1337 participants (RR-0.75, 95% CI: 0.65–0.87). Additionally, the analysis concluded that steroid use might have minimal or no impact on the neurological deficit [40]. The role of adjunctive strategies like aspirin on disability needs further study.

In conclusion, the mortality and morbidity with the currently used regimens are very high despite current treatment regimens. Studies evaluating shorter, more efficacious regimens are urgently needed. We optimize currently available common drugs in this RCT to impact morbidity-free survival in tuberculous meningitis.

